## Abstract

**Background:**

Significant concomitants of the sick role maladaptation in colorectal cancer (CRC) patients include inappropriate cognitions, emotional states, and overt conducts associated to disease. This protocol was developed to implement and evaluate the effects of a self-led, virtual reality-based cognitive behavioral therapy (VR-CBT) on the sick role adaptation among working-age CRC patients.

**Methods:**

This is an assessor-blinded, randomized controlled trail that adheres to the SPIRIT 2013 Statement guidelines. A total of 60 working-age CRC patients will be recruited from the colorectal wards of a cancer center and randomly assigned to the VR-CBT group or attention control (AC) group. The VR-CBT group will receive a 7-sessions VR-CBT targeted to sick role adaptation, while the AC group will receive weekly attention at the same time the VR-CBT group receives the intervention. The sick role adaptation, anxiety and depression, illness perceptions, and quality of life will be measured at baseline, 1, 2 and 3-month after completion of the intervention. Side-effects related to VR in the VR-CBT group will be measured at the end of each session. The participants will receive invitations to participate in semi-structured interviews to explore their experiences with the intervention.

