**Fig. 2 Fig2:**
[figure not shown]
The overview of intervention targets, sessions in perioperative stage and rehabilitation stage, and adopted VR techniques

Based on Unity software (version 2018.3.11fl), we developed a self-led VR-CBT app that included comprehensive components of CBT in collaboration with School of Computer Science and Engineering, Sun Yat-sen University. The desktop VR application, classified as non-immersive in comparison to VR solutions using a head-mounted display, was adopted in this study. The avatars and structures constructing the virtual environment were built using Blender 2.83. The app has been registered in Copyright Protection Centre of China (Certificate No.11288804), and has been licensed by the Ministry of Industry and Information Technology of China (No. ICP 2022124889). The first phase of this app development involved an extensive, iterative process with numerous rounds of user testing. The app is designed with multimodal characteristics, including user-friendly interface, human–computer interaction and VR soundscape (therapeutic music, sound of waves, seagulls, footsteps, etc.) to strengthen immersion. Participants can interact in first-person perspective with the dynamic high-fidelity virtual environment by acting as a mouse pointer. Figure 3 shows the visual representations of the app content. Participants will be asked to install the app on their smartphones for free and instructed to use the app by the research nurse and provided with a user guide to introduce the functions in the app and provide solutions to problems, noting that the sessions should be completed in order and that each subsequent session will become available when the preceding one completed. Each participant will be assigned a unique key to login the app, while AC group will have no access to login to avoid contamination.

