	3 (2 weeks post-surgery)	Confrontation rather than avoidance	• Health education on enterostomy self-care or Kegel exercises • Effective behavioral strategies for adapting to the sick role • Appliance of behavioral experimental techniques to validate strategies • Key points summary and quiz • Homework assignment: Patients perform behavioral experiment and record results	
Rehabilitation stage	4 (3 weeks post-surgery)	My emotions are under my control	• Health education on physical activities of CRC survivors • Daily activities related to positive emotions • Muscle relaxation technique with real-time assessment • Key points summary and quiz • Homework assignment: Patients record the use of muscle relaxation technique	
	5 (4 weeks post-surgery)	Think it in a different way	• Health education on nutrition and dietary of CRC survivors • Psychoeducation of irrational illness and role beliefs • Key points summary and quiz • Homework assignment: Patients record the irrational and rational illness beliefs	
	6 (5 weeks post-surgery)	Actions speak louder than words	• Health education on health promotion behaviors of CRC survivors • Problem solving to the role maladaptation, including goal setting and time allocation • Key points summary and quiz • Homework assignment: Patients record behaviors that aim to adapt to the sick role	
	7 (6 weeks post-surgery)	Review and cope in the future	• Health education on follow-up visits of CRC survivors • Review the change of emotion, cognition, behaviors and CBT technique in the intervention • Gratitude to the participants and encouragement of coping in the future with CBT techniques	SSQ, semi-structured interviews

A master of Nursing Specialist who has undertaken the CBT training will monitor the adherence to the app protocol by tracking the number of sessions and homework that participants accessed in the backstage of app. Additionally, the intervention nurse will be responsible for checking the completion of patients submitted homework. More importantly, the intervention nurse will be tailored to address the issues patients encountered in completing homework.

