The most common side effect associated with VR is simulator sickness, or VR sickness, cybersickness. It is a symptom similar to motion sickness that may manifest both during and after exposure to various VR environments, such as headaches, dizziness, and nausea during and after using VR devices [39, 40]. To reduce simulator sickness, we have paid extra attention to the various aspects of a VR system that contributed to users’ discomfort while designing the system. First, the app is based on desktop VR technique which is non-immersive and has the least potential for arising motion sickness. Second, the environment in VR-CBT app do not overly emphasize fast movement or rotation, and participants will have full control of their own motion in the VR environment. Third, to decrease the risk of dizziness, before entering the VR environment, the system will send prompt messages automatically to remind patients to avoid excessive movement or sudden head movements. Furthermore, we have increased and stabilized the frame rate (from 30 Frames Per Second to 60 Frames Per Second) to reduce the potential for dizziness, as the high display frame refresh rate is considered a crucial approach for alleviating the dizziness in VR applications [41]. In addition, the app improves the stability of VR scenario to reduce camera jitter or position changes that may cause dizziness.

Several strategies will be adopted to prevent attrition of study participants. Messages via WeChat will be sent weekly to keep in touch with patients after discharge. In addition, in the case of failure to reach participants, their main caregivers will be contacted. Incentives will be offered to all participants to expresses our gratitude when evaluating outcome variables at baseline, 1, 2 and 3-month post-intervention.

The intervention will be terminated if the participant declares he or she no longer wishes to participate, or is unable to continue the protocol treatment owing to adverse events. If the intervention proves to be effective, the VR-CBT app will be free available for participants enrolled in the AC group. Project management group meeting will be conducted weekly and blind information on the study.

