### Other measurements

The socio-demographic and clinical characteristics of the participants will be collected, such as sex, age, educational level, marital status, household income per month, tumor location, stage and treatment modality.

Furthermore, semi-structured interviews will be employed to explore and gain insights into participants’ experiences and perceptions of the VR program until data saturation. The post-intervention interviews will be carried out following the completion of the final scheduled session and audio recorded after obtaining informed consent from the participants. Open-ended, probing questions will be used to guide the interview (Table 2). Content analysis approach will be applied to analyze the qualitative data.

**Table 2 Tab2:** Topic guide for post-intervention interview

1. When do you usually use the app? Why? 2. How do you feel about VR program? 3. What impressed you most in the VR program? 4. How the VR program help you adapt to the sick role and cope with CRC? 5. Have you experience any discomfort or difficulties during the usage of the VR program? Please tell me details. 6. What are your thoughts on the homework? 7. What advice would you give us on the VR program? 8. If there is a chance, would you recommend the VR program to other patients? Why?	

In addition, login counts and time, length of usage, time spent of each session, quiz results and results of human–computer interaction will be collected via backend monitoring data to evaluate the completion of the intervention. On the other hand, the privacy issues will also be seriously taken into account. First, the app will not collect the personal information that may recognize the patient identity such as name, age, residence and diagnosis. Second, the user data will be stored in password-controlled, restricted-access servers in the university to protect user information from loss, misuse, unauthorized access or disclosure, alteration, or destruction. Third, the user behavior data will only be used for statistical analysis and supervised by the Institutional Review Board of School of Nursing, Sun Yat-sen University.

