### Data collection procedure

The Consolidated Standards of Reporting Trials flowchart is presented in Fig. 4. The research nurse who is responsible for participant recruitment and random group assignment will carry out baseline evaluations. Each participant will be required to complete the Chinese versions of the IBQ, HADS, BIPQ, EORTC-QLQ C30 and the socio-demographic questionnaires at colorectal oncology ward. Data collection will be carried out through electronic questionnaires distributed to discharged participants by a research nurse who will remain blinded to the group allocation of the participants. Immediately following the program's final session, another research nurse will conduct semi-structured interviews with the participants in VR-CBT group. If the research nurse fails to reach some participants, their main caregivers will be contacted and remind the participants to complete the follow-up.

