## Discussion

To the best of our understanding, this will be the first randomized controlled trial of a self-led VR-based CBT intervention for working-age CRC patients in China. If the intervention shows promising results and favorable user experience, it will generate new insights to the advancement of theoretical and practical knowledge of CBT interventions which focus on irrational illness belief, negative emotions and ineffective coping styles and aim to promote psychosocial adaptation. Furthermore, it will add to the evidence that self-led VR-based CBT has potential to serve as an accessible and feasible alternative to traditional high-cost treatment and applies in cancer survivorship care settings to improve the quality of patient-centered care and outcomes of younger cancer survivors.

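### The side-effect questionnaire and the interviews are tied to finishing a session and the programme, so the session that makes a participant stop may go unscored and the reason unrecorded

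*Protocol article*

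**What the plan says.** **SSQ timing.** The abstract (Methods) states: "Side-effects related to VR in the VR-CBT group will be measured at the end of each session". The section Side-effect measurement describes the instrument but gives no timing. In Table 1 the SSQ is printed beside session 1 and, as "SSQ, semi-structured interviews", beside session 7. The cells for sessions 2 to 6 are blank, which may be a merged cell lost when the text was extracted.

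**Access to sessions.** Under The VR-CBT intervention, sessions are to be taken in order, and "each subsequent session will become available when the preceding one completed".

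**Interviews.** Other measurements says: "The post-intervention interviews will be carried out following the completion of the final scheduled session". Data collection procedure places them directly after the programme's "final session, another research nurse will conduct semi-structured interviews with the participants in VR-CBT group". The abstract is more general: "The participants will receive invitations to participate in semi-structured interviews to explore their experiences with the intervention". The topic guide in Table 2 includes one question on discomfort or difficulties during use.

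**Stopping.** The VR-CBT intervention section foresees that the intervention ends if a participant withdraws or "is unable to continue the protocol treatment owing to adverse events". No SSQ, interview or reason-for-stopping record is attached to that event.

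**Other records.** Logins, length of use, time per session and quiz results are logged by the app (Other measurements). A nurse specialist tracks the sessions and homework accessed (The VR-CBT intervention).

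**The concern.** The app is self-led. The protocol accepts that simulator sickness can begin during exposure as well as after it, and Limitations names it as a remaining risk. A participant who becomes dizzy or nauseated part-way is likely to close the app. If the SSQ comes only when the session finishes, the exposure that caused the stop is the one least likely to be scored. The sequential lock then removes later scores too, unless the participant returns and completes the abandoned session. The interview, which holds the only open question on discomfort that the article describes, comes after a point that this participant may not reach.

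At stake is how the trial describes the app. The Discussion makes its wider claims conditional on user experience: "If the intervention shows promising results and favorable user experience". It also presents the app as a possible accessible and feasible alternative to traditional treatment. Tolerability and experience data drawn mainly from people who tolerated the sessions are a weak basis for that.

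**Working it through.** The article gives no side-effect rate, so there is no planned figure to recompute for the SSQ itself. The check has three parts.

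**1. What a participant who stops contributes.** Suppose someone abandons session *k* of 7 and does not return.

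| Abandoned session | SSQ scores if taken at each completed session (*k* − 1) | Scores missing (8 − *k*) | SSQ scores if taken at sessions 1 and 7 only |
|---|---|---|---|
| 1 | 0 | 7 | 0 of 2 |
| 4 | 3 | 4 | 1 of 2 |
| 7 | 6 | 1 | 1 of 2 |

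Only someone who abandons session 1 has no score at all. In every row the missing scores include the session that led to the stop. If the Table 1 timing is the intended one, anyone who stops in sessions 2 to 7 has a single score, from session 1, which Table 1 places one week before surgery.

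**2. How many might be affected.** The only relevant figure in the document is the 20% attrition allowance in Sample size and recruitment. Reproducing it: 23 / (1 − 0.20) = 28.75, so 29 per arm and 58 in total, against the stated 30 and 60. That agrees within two participants. Applied to the VR-CBT arm, 0.20 × 30 = 6 might stop and 24 would reach session 7. This borrows an allowance made for the sample size and treats it as a rate of stopping the app, which is an assumption.

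**3. How far a completers-only figure could be off.** Let *s* be the share who stop, *p*_s the share of stoppers with sickness and *p*_c the share of completers with sickness.

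- All-participant rate = *s* × *p*_s + (1 − *s*) × *p*_c
- Understatement = *s* × (*p*_s − *p*_c)

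With *s* = 6/30 = 0.20, and with *p*_s and *p*_c assumed:

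| *p*_c (completers-only figure) | *p*_s | All-participant rate | Understatement (points) |
|---|---|---|---|
| 5% | 5% | 5% | 0 |
| 5% | 20% | 8% | 3 |
| 5% | 50% | 14% | 9 |
| 5% | 100% | 24% | 19 |
| 10% | 10% | 10% | 0 |
| 10% | 20% | 12% | 2 |
| 10% | 50% | 18% | 8 |
| 10% | 100% | 28% | 18 |

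The table treats stoppers as giving no score at all. Where they have scores from earlier completed sessions, and those scores already show symptoms, the understatement is smaller.

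**The case against.** The strongest reply is that this reads silence in a condensed article as exclusion.

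- **End of a session need not mean completion.** A session cut short also ends, and no text says that the SSQ sits inside the app or behind the completion lock. This stands as an ambiguity. Nothing, however, ties the SSQ to an unfinished session, and the plan does not say how a self-led user who closes the app would be reached.
- **A reader might infer that such participants are never measured.** The documents do not support that: scores from earlier completed sessions exist, and the usage logs cover every user. What the logs lack is the reason. They cannot separate nausea from dislike, surgical recovery or lack of time.
- **A reader might infer that interviews are restricted to completers.** No sentence says so. The abstract invites participants generally, and the final scheduled session could mean the calendar point of six weeks after surgery. The wording in Other measurements and Data collection procedure still points to completion, so the choice should be stated.
- **A reader might infer that stopping because of symptoms goes unnoticed for safety.** That does not follow. Ending the intervention for adverse events presupposes that the team learns of them, there is weekly WeChat contact after discharge, and the full protocol, which is not shown, may hold adverse-event procedures.
- **The risk may be low.** The app is non-immersive, and people with past severe motion sickness or vertigo are excluded. Also, the SSQ is neither a primary nor a secondary outcome, and the Discussion speaks of user experience, not of side-effects. The interviews are qualitative and estimate no rate. All of this limits the weight of the point but does not remove the selection in the schedule.

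**Conclusion.** The point holds in a limited form. Followed as written, the schedule can leave the session that made a participant stop without an SSQ score, and that participant's reasons unrecorded. Side-effect and user-experience findings may therefore lean towards those who tolerated the app. This comes from measurement times that the article itself states, not merely from detail left out.

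A reader might go further and say that the app will look safer than it is. The documents do not support that, because they give no rate of stopping and no rate of sickness. The 0 to 19 points above rest on assumed rates, on 20% stopping and on stoppers having no scores. The bias is zero if stopping is unrelated to symptoms or dislike. The primary analysis of sick role adaptation is not affected by this point. It is worth correcting because the remedy is small.

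**What to change.** 1. **SSQ:** state that it is given at any exit from a session, completed or not, and at discontinuation of the intervention. Flag scores from partial sessions so that they can be shown separately.
2. **Reason for stopping:** have the nurse who already tracks sessions add a reason for each unfinished session to that record, with symptoms as a distinct category.
3. **Reporting:** give the number who stopped because of symptoms over all participants randomised to VR-CBT (30 planned), alongside the SSQ scores and the number of participants contributing at each session.
4. **Interviews:** amend Other measurements and Data collection procedure so that participants who stopped early are also invited, for example at discontinuation or at the end of follow-up.
5. **Consistency:** reconcile the abstract's timing with Table 1 so that both show the same SSQ sessions. If the blank cells are only a lost merge, no change is needed there.

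The cost is a change in how the SSQ is triggered, one extra field in the adherence record, a wider interview invitation and slightly more follow-up work. No new staff are needed. The drawback is that some SSQ scores will reflect partial exposure, hence the flag. These are changes to measurement and reporting only; the rule for ending the intervention is left as it is.

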### The VR-CBT intervention

Participants in the VR-CBT group will be asked to complete a 7-sessions VR-CBT via a mobile app added onto standard care. We believe that this format will be more acceptable and available for working-age adults with CRC. The intervention is based on CSM targeted for negative emotions, irrational illness cognition, maladaptive coping strategies and supported by the use of CBT techniques during the intervention. According to psychological characteristics of patents in perioperative and rehabilitation stage, the weekly intervention will sequentially provide techniques of negative emotion adjustment, illness cognition reconstruction, and effective coping behaviors as the sick role at two different stages, from pre-surgery to 6 weeks post-surgery. Each session is estimated to take 40 min to complete. Patients will be allowed to repeat sessions at any time if they want within the intervention weeks. Figure 2 shows the overview of intervention targets, sessions in perioperative stage and rehabilitation stage, and adopted VR techniques.

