### Side-effect measurement

The most widely used measurement of VR related side-effect was the Simulator Sickness Questionnaire (SSQ), developed by Kennedy et al. [50]. The SSQ consists of 16 items with answers ranging from 0 to 3 based on the severity of the participant's symptoms. The SSQ includes three subscales: nausea, oculomotor and disorientation. The overall score serves as an indicator of total severity of the simulator sickness, with a higher the SSQ score indicating more severe simulator sickness [39]. The Chinese version of SSQ showed acceptable structure validity and reliability [51].

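### The Simulator Sickness Questionnaire is taken only after sessions and only in the VR-CBT arm, so its score cannot separate app effects from symptoms already present

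*Protocol article*

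**What the plan says.** All references are to the protocol article.

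- **Timing and arm.** The abstract (Methods) states: "Side-effects related to VR in the VR-CBT group will be measured at the end of each session".
- **Schedule.** Table 1, which covers the VR-CBT intervention only, lists the SSQ beside session 1, one week before surgery. It appears again beside session 7, six weeks after surgery, as "SSQ, semi-structured interviews". The session 1 entry may be a merged cell covering the sessions below it. No pre-session SSQ is shown.
- **Baseline.** Under Data collection procedure: "Each participant will be required to complete the Chinese versions of the IBQ, HADS, BIPQ, EORTC-QLQ C30 and the socio-demographic questionnaires". The SSQ is not in that list.
- **Control arm.** The attention control section describes weekly nurse contact over the same weeks, with general questions about how the patient feels, eats and sleeps. It mentions no SSQ.
- **Reading of the score.** Under Side-effect measurement: "The SSQ includes three subscales: nausea, oculomotor and disorientation". The same section says "The overall score serves as an indicator of total severity of the simulator sickness", with "a higher the SSQ score indicating more severe simulator sickness".
- **Symptoms attributed to VR.** The section on the VR-CBT intervention describes VR sickness by symptoms "such as headaches, dizziness, and nausea during and after using VR devices".
- **Period.** The sessions run "from pre-surgery to 6 weeks post-surgery".

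**The concern.** The SSQ, as described, grades symptoms; nothing in its description asks the patient what caused them. The symptoms named are non-specific, and patients recovering from bowel surgery can have them without opening an app. If a patient is already nauseated when the session starts, the post-session score carries that nausea, and the protocol's reading of the total assigns it to simulator sickness.

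At stake is the trial's only structured measure of the adverse effect that its Limitations section singles out. A reader of the results could not tell whether a raised score reflects the app or the patient's condition that week. The problem cannot be repaired in the analysis, because a pre-session score that was never collected cannot be recovered.

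**Working it through.** The plan states no figure on this point, so there is none to reproduce. The check is of what the described measurements can identify.

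**1. What a post-session score contains.** For one patient at one session, let B be the symptom score just before the session, V the change caused by the app, and Y the post-session score:

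Y = B + V

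Only Y is collected. Any split between B and V fits the same Y, so V is not identified unless B is known or can be taken as zero.

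**2. Can B be taken as zero?** Session 1 is one week before surgery. Sessions 2 to 7 are at one, two, three, four, five and six weeks after it (Table 1), so 6 of 7 sessions (86%) fall in the postoperative weeks. The exclusion of past severe motion sickness or vertigo (Sample/participants) limits susceptibility to VR sickness, but not symptoms from surgery or its treatment.

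**3. Can B be estimated from anything else collected?**

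| Source | Why it does not supply B |
|---|---|
| SSQ at session 1 | Before surgery, but still after app use |
| Baseline questionnaires | SSQ not among them |
| Weekly control-arm contact | General questions, no SSQ |
| QLQ-C30 nausea/vomiting scale | Both arms, but at baseline and one, two and three months after the intervention, not around sessions |
| Interview question 5 (discomfort) | VR-CBT interviewees only, qualitative, after the last session |

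None gives a pre-session symptom level.

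**4. How many scores are involved.** These are ceilings, with 30 patients in the arm and every session completed.

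- SSQ after every session (abstract): 30 × 7 = 210 scores, of which 30 × 6 = 180 postoperative.
- SSQ at sessions 1 and 7 only (Table 1 as it reads in the text): 30 × 2 = 60 scores, of which 30 postoperative.

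The planned 20% attrition would lower both.

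**5. Illustration of scale, on assumptions not in the documents.** Suppose the app has no effect, sessions are independent, and a patient has some SSQ symptom at any given session with probability q. The chance of at least one non-zero SSQ over k sessions is 1 − (1 − q)^k.

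| q (assumed) | k = 7 | of 30 | k = 2 | of 30 |
|---|---|---|---|---|
| 0.05 | 30% | 9 | 10% | 3 |
| 0.10 | 52% | 16 | 19% | 6 |
| 0.20 | 79% | 24 | 36% | 11 |
| 0.30 | 92% | 28 | 51% | 15 |

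For example, with q = 0.10 and k = 7: 1 − 0.9^7 = 0.52, and 0.52 × 30 is about 16. Positive correlation between sessions would lower these shares. The table counts any non-zero score and says nothing about severity. Its only use is to show that the answer depends almost wholly on q, which the design does not measure.

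**6. What a pre-session score would change.** With B collected, D = Y − B = V, apart from any unrelated change during the session itself, which is planned at about 40 minutes. Recovery over weeks then drops out of the comparison.

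**The case against.** The strongest reply is that this matters little. The SSQ is neither a primary nor a secondary outcome and is absent from the hypotheses, and no stopping decision in the document depends on an SSQ score. The app is non-immersive, with design measures against dizziness, and susceptible patients are excluded. A bias that overstates side-effects is cautious from a safety standpoint. How SSQ scores are summarised may also be set out in a fuller document. Most of this stands, and it limits the weight of the point. It does not remove the point: the article fixes when and in whom the SSQ is taken and how the total is read, and no later summary can supply a score that was not collected.

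Stronger readings are tempting, and the documents do not support them.

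- *A reader might infer that postoperative symptoms will be counted as VR side-effects.* The article sets no threshold, event definition or attribution rule for the SSQ. What follows is only that such symptoms cannot be distinguished from app effects.
- *A reader might add fatigue or adjuvant treatment as sources of distortion.* The article names fatigue as a QLQ-C30 scale, not as an SSQ symptom, and does not say that adjuvant treatment falls in these weeks.
- *A reader might put a number on the false signals.* Any such number is an assumed rate multiplied by a ceiling; nothing in the documents anchors the rate.
- *A reader might argue that recovery over the weeks would hide a real app effect.* That requires the SSQ trend to be used as evidence about VR, and no such analysis is described.

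**Conclusion.** The point holds as a weakness of a stated measurement design. Followed as written, the SSQ total cannot separate an effect of the app from nausea, dizziness or headache already present before the session, and this applies to the six sessions in the postoperative weeks in particular.

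The conclusion rests on two things: the article describes no pre-session, baseline or control-arm SSQ, and some patients have such symptoms in the weeks after surgery for other reasons. The second is an assumption about the population, and its extent is not given. The size of the distortion is therefore unknown. The uncertainty over whether Table 1 means every session or only sessions 1 and 7 changes the number of scores affected, not the conclusion. The primary outcome and the between-arm comparisons are not touched. The change is worth making because it is cheap and must be in place before sessions begin.

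**What to change.** 1. Wherever a post-session SSQ is taken, have the app present the same 16 items immediately before the session. If that is too much, do so at least at session 1 and at selected postoperative sessions.
2. Define the VR side-effect measure as the post-session score minus the pre-session score, within patient and session.
3. Report the raw post-session total descriptively, as symptom level after use rather than as simulator sickness.

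The cost is one extra 16-item self-report screen per measured session, an estimated one to two minutes for the patient. No additional staff or participants are needed. The burden falls on perioperative patients, which is the reason for allowing selected sessions. The difference score would still include any non-VR change during the session, but that is a much smaller gap than having no starting value.
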